### Safety and AE Monitoring

In this study, safety will be monitored by clinical research associates including AEs, serious AEs, withdrawals or treatment modification due to AEs, vital signs and physical examinations, routine blood and urine tests, liver and kidney function tests, blood coagulation function test, fasting glucose test, 12-lead electrocardiogram, and concomitant medications for management of AEs. The severity of AEs will be graded using CTCAE version 3.0. The indexes and time points for data collection are shown in **Table 3**.

### Sample Size Estimates

This trial is a pilot study. Based on the superiority clinical trial hypothesis test sample size estimation (Sakpal, 2010) and data from preliminary observations and case-control studies (Sun, 2010; Wan et al., 2015; Cheng et al., 2019), we assumed that over a 28-day period, the minimum difference of NIHSS score between the experimental and placebo groups would be 0.95. With a 2-year enrollment period and 180-day follow-up period, taking into account a 20% dropout rate, we predicted that a total of 160 participants would achieve 80% power and a two-sided 5% significance level. Therefore, according to the ratio of 1:2:1:1, we will recruit 64 patients in experimental group 2 and 32 patients each for experimental groups 1 and 3, and the placebo control group.

### Statistical Analysis Plan

Statistical analysis will be performed using SPSS version 15.0 for Windows (Chicago, IL, USA). Professional statisticians who are independent of all the other processes of the study will perform the statistical analyses. Consistent with the CONSORT statement and intention to treat principle, the last observation carried forward method will be used for missing values. Cases in the per protocol set (PPS) are those who thoroughly adhere to the protocol without absence of baseline characteristics. Analyses of the primary outcome and curative effect will be carried out using a full analysis set approach and PPS approach. The safety analysis set will include all randomized patients who have completed at least one study visit. Participating centers will be required to count the number of participants in each center and list those who are removed from the PPS. For quantitative data, we will calculate the mean, standard deviation, median, minimum, maximum, lower quartile (Q_1_), upper quartile (Q_3_); and for qualitative data, we will describe numbers and percentages. Inter-group comparisons will be analyzed by appropriate methods: independent t-tests (homogeneity of variance, normal distribution) or Wilcoxon rank-sum test for quantitative data, chi-square test or Fisher’s exact test (if chi-square test is not applicable) for qualitative data, and Wilcoxon rank-sum test or Cochran-Mantel–Haenszel test for ranked data. *P* <0.05 will be considered statistically significant.

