### Outcome Measures

#### Primary Outcome

The primary outcome will be the NIHSS score, which is commonly used to evaluate neurological recovery and quality of life in clinical practice (Yaghi et al., 2016). The NIHSS score will be measured at the end of the 28-day treatment period and compared with baseline, and changes will be compared between groups (**Table 3**).

**Table 3 T3:** Measurement items and time line.

Visit	Screening	Intervention	Follow-up	
	V1	V2	V3	V4
Unit:day	-7-0	28 ± 4	90	180
Screening the subject	×			
Informed consent form	×			
Demographic information	×			
Inclusion/exclusion criteria	×			
Get the random number	×			
Previous medical history and allergy history	×			
Concomitant diseases and treatment history	×			
Connect to the Internet hospital “Doctor Tao” platform	×			
Head CT/MRI	×**^#^**			
Urine pregnancy test (HCG)	×**^*^**			
Vital signs^1^ and physical examination	×	×		
Blood routine^2^	×	×		
Urine routine	×	×		
Liver^3^ and kidney^4^ function	×	×		
Blood coagulation function^5^	×	×		
Fasting glucose	×	×		
12-lead electrocardiogram	×	×		
NIHSS	×	×	×	
TCM symptom score	×	×	×	
mRS score	×	×	×	
Barthel Index	×	×	×	
Biological effect indicators	×	×		
Metabolic and proteome data	×	×		
Pharmacokinetic index	×			
Drug distribution	×			
Recovery drug		×		
Record adverse events		×		×
Record drug combination		×		×
Compliance prediction		×		

^#^if imaging examination shows typical lesions after the onset and 4 weeks prior to the study can be avoided.

^*^Only women of child-bearing age were tested before the trial.

^1^Vital signs including the temperature, heart rate, respiration, blood pressure.

^2^Blood routine tests including red blood cells, hemoglobin, white blood cells, and platelets.

^3^Liver function tests including alanine and aspartate aminotransferases, alkaline phosphatase level, total bilirubin, and gamma-glutamyl transferase.

^4^Kidney function tests including creatinine and blood urea nitrogen.

^5^Blood coagulation function tests including prothrombin time, activated partial thromboplastin time, thrombin time, and fibrinogen.

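### With no NIHSS visit between baseline and day 28, LOCF carries the baseline score forward and sets the primary change to zero for any patient without a day-28 score

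*Protocol article*

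**What the plan says.** The Statistical Analysis Plan section invokes CONSORT and intention to treat, and then fixes one rule: "the last observation carried forward method will be used for missing values". It names no other missing-data method. The primary outcome is analysed in both a full analysis set and a per-protocol set.

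The Primary Outcome section says: "The NIHSS score will be measured at the end of the 28-day treatment period and compared with baseline, and changes will be compared between groups". In Table 3 the NIHSS row is marked at V1 (day -7 to 0), V2 (day 28 ± 4) and V3 (day 90), and nowhere else.

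The Sample Size Estimates section assumes that "the minimum difference of NIHSS score between the experimental and placebo groups would be 0.95". It states the loss to follow-up in a sentence that also gives the 180-day follow-up, "taking into account a 20% dropout rate", and concludes that "a total of 160 participants would achieve 80% power and a two-sided 5% significance level". The split is 32/64/32/32. No SD is given.

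**The concern.** LOCF needs an earlier post-baseline value to carry. For the primary endpoint none is scheduled, so the rule reduces to baseline carried forward, even for a patient who misses day 28 and returns at day 90.

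Zero change is a poor guess in this population. The inclusion criteria require a disease course of 1–4 weeks and an NIHSS of 4–20, and every arm receives guideline-based basic treatment. A patient who worsens or dies before day 28 also enters the NIHSS analysis as unchanged.

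Three things are at stake: the size of the primary estimate, its power, and, if missingness differs between arms, its type I error.

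**Working it through.** **Inputs from the article.** Difference 0.95; two-sided 5%; 80% power; 20% dropout; 32/64/32/32 randomised.

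**Assumptions, because the article is silent.** The SD of change; the mean placebo improvement m (0 to 3 points); the share d missing at day 28 (5%, 10%, 20%).

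**1. The plan's own figure.** 160 × 0.80 = 128 evaluable, or 25.6 in each small arm and 51.2 in the NXTC arm. This is internally consistent, but 160 cannot be reproduced without an SD. The SD that gives a t-test 80% power for 0.95 at 25.6 v 25.6 is 1.19. It is used below as an assumption.

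**2. Dilution, equal missingness unrelated to outcome.** The expected difference is (1 − d) × 0.95:
- 5%: 0.95 × 0.95 = 0.90
- 10%: 0.90 × 0.95 = 0.855
- 20%: 0.80 × 0.95 = 0.76

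This step needs no SD.

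**3. Power.** Carrying zeros forward also adds variance. For an arm with mean improvement μ among those observed, variance = (1 − d)·SD² + d(1 − d)·μ², with μ = m on placebo and m + 0.95 on active drug. Power ≈ Φ(difference/SE − 1.96), 32 v 32.

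Example, d = 20%, m = 2:
- placebo variance 0.8 × 1.416 + 0.16 × 4 = 1.773
- active variance 0.8 × 1.416 + 0.16 × 8.70 = 2.525
- SE = √((1.773 + 2.525)/32) = 0.366
- 0.76/0.366 = 2.07, so power is about 55%

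| Missing at day 28 | m = 0 | m = 1 | m = 2 | m = 3 | Observed cases only |
|---|---|---|---|---|---|
| 5% | 87% | 85% | 80% | 74% | 88% |
| 10% | 85% | 80% | 71% | 60% | 86% |
| 20% | 79% | 69% | 55% | 41% | 81% |

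The last column is Φ(0.95/(1.19·√(2/n)) − 1.96) with n = 30.4, 28.8 and 25.6. It uses the same approximation and shows how much of the loss comes from the zeros rather than from lost patients. The 20% entry is 81.5% rather than 80% because the SD was solved with a t-test.

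**4. Unequal missingness, no drug effect (illustration).** With 15% missing in one arm and 25% in the other and m = 3, the arm means are 0.85 × 3 = 2.55 and 0.75 × 3 = 2.25, a false difference of 0.30. The variances are 0.85 × 1.416 + 0.1275 × 9 = 2.351 and 0.75 × 1.416 + 0.1875 × 9 = 2.750. SE = √(5.101/32) = 0.399 and z = 0.75. The two-sided rejection rate is about 12% instead of 5%. At m = 2 the false difference is 0.20 and the rate about 9%; at m = 1, 0.10 and about 6%. Swapping the arms reverses the sign.

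**The case against.** - **When dropout occurs.** A reader might infer that every dropout is scored as zero change. That is not so: a patient who leaves after day 28 keeps the observed score. The 20% is given beside the 180-day follow-up, so it need not all fall before day 28. With 5% missing, 80% power is kept up to about 2 points of placebo recovery. This stands, and it is why the result is given as a range.
- **The SD is back-solved for one contrast.** This also stands. The 32 v 64 contrast implies about 1.40, and power at 20% missing is then 79/73/61/48% for m = 0 to 3. With an assumed SD of 3, power is about 20% on observed cases and 20/20/19/17% under LOCF, so the relative loss is small. That shows sensitivity to the SD, not adequate power. The dilution in step 2 is unaffected.
- **Unequal missingness is hypothetical.** The trial is double-blind and double-dummy with 28 days of treatment, and nothing in the article predicts a 15% v 25% split. The direction and mechanism stand; the size is illustrative.
- **Harm is hidden.** A reader might infer this from deaths and worsening being scored as unchanged. The Safety and AE Monitoring section collects AEs, serious AEs and withdrawals due to AEs, so such harm is missing from the NIHSS estimate but not from the trial.
- **The per-protocol analysis guards against it.** It does not, because that set selects on adherence after randomisation.
- **The full plan may settle it.** The article does not define the full analysis set. If membership required a post-baseline NIHSS, many patients without day 28 would be excluded rather than imputed. One seen only at day 90 would still have baseline carried forward. Handling of deaths and further sensitivity analyses may properly sit in the unseen plan and are not counted as missing. LOCF itself is a stated choice.
- **It is a pilot.** The article nonetheless claims a superiority test with 80% power.

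**Conclusion.** The concern holds for patients without a day-28 NIHSS. From the visit schedule and the stated rule alone, LOCF is baseline carried forward for the primary endpoint, and zero change is implausible at 1–4 weeks after stroke.

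Under equal missingness unrelated to outcome, 0.95 becomes 0.90, 0.855 or 0.76 with 5%, 10% or 20% missing, the last being an upper figure. Power under LOCF ranges from about 87% (5% missing, no placebo recovery) to 41% (20% missing, 3 points), given the back-solved SD of 1.19 and 32 v 32. Under unequal missingness the bias can go either way and the type I error can exceed 5%, so LOCF cannot be defended as simply conservative.

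The article does not support reading 0.76 or 41% as the expected result.

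**What to change.** In the Statistical Analysis Plan section, replace LOCF as the primary method for the full analysis set with one of:

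- multiple imputation followed by ANCOVA on day-28 NIHSS, with baseline NIHSS and centre as covariates; or
- a likelihood-based repeated-measures model of the scheduled NIHSS visits, with baseline NIHSS as a covariate and the day-28 contrast as primary.

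Keep LOCF at most as a sensitivity analysis. A rank-based treatment of deaths and a delta-adjusted analysis are optional additions.

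The repeated-measures model has a limit. A patient lost before day 28 will often lack day 90 too, and then contributes no post-baseline score. If it is chosen, state whether day 90 counts from randomisation or from onset, since the Secondary Outcomes section times its day-90 comparisons from onset.

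The cost is a revised paragraph, some extra analysis work and possibly software other than SPSS 15.0, the named analysis package; the article mentions SAS 9.4 only for randomisation. No new visits, data or patients are needed.

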## Methods and Design

### Trial Design

This trial will be a multicenter, randomized, double-blinded, placebo-controlled intervention study of IS with QDBS syndrome, followed by an add-on of Chinese patent medicine. It is designed to evaluate the efficacy and safety of BHG, NXTC, and YTG for treating IS with QDBS syndrome. The patients will be randomly allocated to four parallel treatment groups using a 1:2:1:1 ratio.

This trial is registered in the Chinese Clinical Trial Registry (No. ChiCTR1800015189) and is in full compliance with the principles of the Declaration of Helsinki and Good Clinical Practice (GCP) guidelines. The protocol has been designed according to the following Standard Protocol Items: Recommendations for Interventional Trials (SPIRIT) checklist and the Recommendations for Interventional Trials and 2013 statement for herbal interventions (Chan et al., 2013a; Huang et al., 2019). We will rigorously follow the latest Consolidated Standards of Reporting Trials (CONSORT 2017) for Chinese herbal medicine recommendations (Cheng et al., 2017). The multicenter clinical trial will be conducted at seven hospitals in China (**Table 2**), and a total of 160 participants will be recruited. After the participants have provided informed consent, they will be enrolled in the trial, which consists of a 28-day treatment period and a 180-day follow-up period. The schematic diagram of study procedures is illustrated in **Figure 1**.

**Table 2 T2:** Hospitals participating in this trial.

Code	Participating hospitals
01	Neurology Department, First Affiliated Hospital of Zhejiang Chinese Medical University
02	Neurology Department, Second Affiliated Hospital of Zhejiang Chinese Medical University
03	Encephalopathy Clinic, Hangzhou Xiaoshan District Hospital of Traditional Chinese Medicine
04	Neurology Department, Huai’an Second People’s Hospital
05	Neurology Department, Third People’s Hospital of Huzhou
06	Encephalopathy Clinic, Luohe Hospital of Chinese Medicine
07	Encephalopathy Clinic, Jinzhou Hospital of Chinese Medicine

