### Inclusion Criteria

Patients will be recruited for this study if they meet all of the following criteria: (1) 40 ≤ age ≤ 80 years, (2) consistent with the western and Chinese medicine diagnostic criteria of IS, (3) meet the diagnostic criteria of TCM symptom differentiation (QDBS syndrome), (4) imaging (computed tomography or magnetic resonance imaging) confirmed anterior circulation infarction (Oxfordshire Community Stroke Project clinical classification of complete or partial anterior circulation infarction), (5) course of disease of 1–4 weeks, (6) 4 ≤ National Institute of Health Stroke Scale (NIHSS) score ≤ 20, (7) first attack or previous history of cerebral infarction but without disability before this attack (modified Rankin Scale [mRS] score ≤1), and (8) signed informed consent.

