### Randomization and Blinding

Central randomization will be performed using stratified and permuted blocks. According to the randomized clinical study program, with the help of the SAS 9.4 statistical software package PROC PLAN process, a stratified randomization method will be adopted to list the random coding table and generate the random arrangement of subjects’ treatment. Patients will be randomized in blocks of varying sizes within each center and stratified by centers.

All eligible participants will be randomly divided into the experimental group 1 (BHG group), experimental group 2 (NXTC group), experimental group 3 (YTG group), and placebo control group using a 1:2:1:1 ratio. According to the randomized clinical study program, the randomized code of the trial drug by statistical experts is the unique identification code of participants. Considering that the dosage forms include granules and capsules, a double-blind and double-simulation design will be adopted. All the participants, researchers, research assistants (conducting interviews with the participants), laboratory and inspection staff, and statisticians will be blinded to treatment assignment until the study is completed.

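### The primary NIHSS comparison is stated as an unadjusted t-test or rank-sum test: valid, but less precise than a model with baseline and centre, and not one fixed test

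*Protocol article*

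**What the plan says.** Under Primary Outcome, the protocol article states: "The NIHSS score will be measured at the end of the 28-day treatment period and compared with baseline, and changes will be compared between groups". The visit schedule in Table 3 plans NIHSS at screening (V1) and at day 28 (V2), so both values are planned for every patient. Entry is limited to "4 ≤ National Institute of Health Stroke Scale (NIHSS) score ≤ 20" (Inclusion Criteria).

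The Statistical Analysis Plan section gives one general rule, opening with "Inter-group comparisons will be analyzed by appropriate methods". For quantitative data it lists "independent t-tests (homogeneity of variance, normal distribution) or Wilcoxon rank-sum test for quantitative data", with no covariate and no stratum. The only method named that can be stratified is in "Wilcoxon rank-sum test or Cochran-Mantel–Haenszel test for ranked data"; it is reserved for ranked data and no stratum is given. Elsewhere in that section, centre is used only for counting participants and listing removals from the per-protocol set.

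Randomization and Blinding says: "Patients will be randomized in blocks of varying sizes within each center and stratified by centers". Trial Design gives seven hospitals. Sample Size Estimates works from a minimum NIHSS difference of 0.95 points, 80% power, two-sided 5%, 20% dropout and 160 patients (32 / 64 / 32 / 32).

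**The concern.** Taken together, these sections imply a two-sample test on change scores. Three things follow.

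- **Baseline is subtracted, not adjusted for.** Subtraction is as efficient as covariate adjustment only if the slope of day-28 on baseline NIHSS is exactly 1.
- **Centre is left out.** Stratified randomisation balances arms within centres. If centre predicts outcome, a test that ignores it keeps between-centre variation in its error term, so its standard error is too large.
- **No single test is fixed.** A t-test addresses a difference in means and a rank-sum test a shift in ranks. The sample size rests on a mean difference of 0.95 points, which a rank-sum test does not estimate.

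At stake is precision in arms of 32, and a clear statement of what the primary result estimates.

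**Working it through.** **Inputs from the article:** difference 0.95; power 80%; two-sided 5%; dropout 20%; 32 placebo and 64 NXTC patients, hence 25.6 and 51.2 evaluable; 32 each for BHG and YTG, hence 25.6 evaluable; seven centres.

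**Inputs not given, so assumed:** the SD of the change, back-solved below; the correlation r between baseline and day-28 NIHSS, taken as 0.5, 0.7 or 0.9; and the share of variance due to centre, taken as 1%, 5% or 10%.

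**1. The plan's own figure.** The total of 160 can be neither reproduced nor refuted, because no SD is stated. Solving backwards for NXTC versus placebo:

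SD = 0.95 / [(1.960 + 0.842) × √(1/25.6 + 1/51.2)] = 0.95 / (2.802 × 0.2421) = 1.40

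If the 80% referred instead to BHG or YTG versus placebo, the implied SD would be 1.21; for all active arms pooled versus placebo, 1.54. The power figures below use 1.40.

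**2. ANCOVA against the change score.** With common SD s at both times:

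- Var(change) = 2s²(1 − r)
- Var(ANCOVA) = s²(1 − r²)
- Ratio = (1 + r)/2

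The direction does not depend on equal variances. With baseline SD a and day-28 SD b, the change-score variance minus the ANCOVA variance is a² + b² − 2rab − b²(1 − r²) = (a − rb)². This is never negative, and is zero only when the slope rb/a equals 1.

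**3. Effect on power.** Power = Φ[0.95 / (1.40 × √ratio × √(1/n₁ + 1/n₂)) − 1.960].

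| Assumed r | Variance ratio | N with the precision of 160 | NXTC vs placebo (80% with t-test) | BHG or YTG vs placebo (68% with t-test) |
|---|---|---|---|---|
| 0.5 | 0.75 | 120 | 90% | 80% |
| 0.7 | 0.85 | 136 | 86% | 75% |
| 0.9 | 0.95 | 152 | 82% | 70% |

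**4. Centre.** If centre explains 1%, 5% or 10% of the change-score variance, removing it multiplies the error variance by 0.99, 0.95 or 0.90. Power for NXTC versus placebo then rises from 80% to about 80.4%, 82.0% or 84.0%.

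**5. Simulation check** (normal data; 26 versus 51 patients spread evenly over seven centres; centre 5% of day-28 variance; 2,000 runs per cell). Power:

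| r | t-test | t-test or rank-sum, chosen by pre-test | ANCOVA | ANCOVA plus centre |
|---|---|---|---|---|
| 0.5 | 81% | 80% | 90% | 91% |
| 0.7 | 81% | 81% | 87% | 88% |
| 0.9 | 85% | 85% | 86% | 92% |

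With no treatment effect, the t-test rejected in 3.9%, 3.7% and 2.7% of runs, below the nominal 5%. ANCOVA plus centre rejected in 4.7%, 4.6% and 5.0%. The r = 0.9 row exaggerates the role of centre: 5% of day-28 variance is 0.05 / [2(1 − r)] of the change-score variance, which is 5% at r = 0.5, 8% at r = 0.7 and 25% at r = 0.9.

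**The case against.** The strongest objection is that the article gives a generic list for all quantitative data, does not name NIHSS in it, and refers in its abstract to a predefined analysis plan that is not shown. Covariates and centre terms are often left to that plan. This limits the point: the unseen plan may already contain an adjusted model. It does not remove it, because the article names specific tests, its primary outcome falls under them, and a better method than the one named is available.

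Four stronger readings are tempting and should not be made.

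- **That baseline NIHSS is ignored.** It is not: the outcome is a change from baseline.
- **That the test is chosen after looking at the data.** The article states conditions for the t-test but no formal pre-test, threshold or timing, and statisticians stay blinded until the study is completed. In the simulation, choosing by pre-test cost almost nothing (null rejection 2.9% to 4.1%). What stands is that one primary test is not fixed.
- **That the unadjusted result is biased or has inflated type I error.** Under randomisation it is unbiased on average, and leaving out centre makes the test conservative.
- **That chance baseline imbalance could shift the result by about a third of the target.** A reader might assume a baseline SD of 4 and a slope of 0.7. The 32-versus-32 baseline difference then has SD 4 × √(2/32) = 1.0, and the shift is 0.3 × 1.0 = 0.3 points, 32% of 0.95. But SD 4 with r = 0.7 gives a change SD of 4 × √0.6 = 3.10 and about 24% power for NXTC versus placebo, which contradicts the stated 80%. With the implied change SD of 1.40, the baseline SD is 1.40/√0.6 = 1.81, the imbalance SD is 0.45 and the shift is 0.14 points, about 14% of 0.95.

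It is also fair that the centre gain is small unless centre matters, and that the article calls the trial a pilot.

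**Conclusion.** The point holds as one of efficiency and definition. The stated comparison is valid on average, but it is less precise than covariate adjustment unless the slope on baseline is 1, it is conservative if centre predicts outcome, and it is not tied to one estimand.

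The size is a variance reduction of 25%, 15% or 5% at r = 0.5, 0.7 or 0.9, assuming equal variances. This does not depend on the SD. The power figures do: they assume that the stated 80% belongs to NXTC versus placebo with a change SD of 1.40. The documents give neither r nor any centre effect, so the direction is secure and the size is not. The change is worth making because it is free; the plan is not invalid without it.

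**What to change.** Name one primary analysis: a linear model (ANCOVA) of day-28 NIHSS on arm, baseline NIHSS and centre, reporting adjusted mean differences with 95% confidence intervals. This keeps the result on the scale of the 0.95-point target. Fix the rule for pooling small centres before unblinding. Keep a centre-stratified rank test as a sensitivity analysis only, so that it cannot replace the primary result. If the unseen analysis plan already specifies such a model, bring the article's wording into line with it.

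The cost is wording. Baseline NIHSS and centre are already recorded. The model spends one degree of freedom on baseline and at most six on centre, out of about 77 evaluable patients (25.6 + 51.2) in the NXTC–placebo comparison alone.

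### The rule for quantitative outcomes offers no unequal-variance t-test, so in the three 2:1 comparisons with NXTC neither listed test holds 5% for a difference in means when the arms differ in spread.

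*Protocol article*

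**What the plan says.** The Statistical Analysis Plan section of the protocol article gives one rule for comparing quantitative data between groups: "independent t-tests (homogeneity of variance, normal distribution) or Wilcoxon rank-sum test for quantitative data". The bracket makes equal variances and normality conditions of the t-test, and the rank-sum test is the only other method named. The section does not say in words what happens when only the variances differ. The natural reading is a switch to Wilcoxon. The threshold is P "<0.05 will be considered statistically significant".

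The rule covers the primary outcome (NIHSS change to day 28) and, as quantitative data, the Barthel Index and TCM symptom scores.

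Sample Size Estimates fixes the arm sizes: "we will recruit 64 patients in experimental group 2 and 32 patients each for experimental groups 1 and 3, and the placebo control group", "taking into account a 20% dropout rate". The planned effect is that "the minimum difference of NIHSS score between the experimental and placebo groups would be 0.95", at "80% power and a two-sided 5% significance level". No SD is given for any arm.

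**The concern.** The pooled t-test estimates one common variance. The rank-sum test takes its null variance from the assumption that both arms have the same distribution. Neither corrects for a difference in spread. With equal arms the resulting errors largely cancel; at 2:1 they do not. If the smaller arm is the more variable one, the test rejects too often for a null of equal means. If the larger arm is, it rejects too rarely.

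Three of the six pairwise comparisons are 2:1: NXTC against placebo, BHG and YTG. NXTC is the largest arm, so a miscalibrated test there affects the comparisons that carry most of the trial's information. A drug that helps some patients and not others widens the spread in its own arm. For NXTC against placebo, this makes NXTC the more variable arm and costs power for the planned 0.95 points.

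**Working it through.** **Inputs.** From Sample Size Estimates: arms of 64 and 32, 20% dropout, a difference of 0.95, 80% power, two-sided 5%. Evaluable numbers: 64 × 0.8 = 51.2 and 32 × 0.8 = 25.6, so about 51 v 26. The SD and the SD ratio between arms are assumptions.

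**The plan's own figure.** The total of 160 cannot be reproduced without an SD. Solving backwards with SD = 0.95 / [(1.960 + 0.842) × √(1/n1 + 1/n2)]:
- 51 v 26: 0.95 / (2.802 × 0.2410) = 1.41 (1.40 with the t distribution).
- 26 v 26: 0.95 / (2.802 × 0.2774) = 1.22 (1.21 with the t distribution).

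**Why 2:1 matters, shown for the pooled t-test.** Let the less variable arm have SD 1 and the other SD 2.
- NXTC less variable: true variance of the difference = 1/51 + 4/26 = 0.1735. Pooled variance = (50 × 1 + 25 × 4)/75 = 2, and 2 × (1/51 + 1/26) = 0.1161. The standard error is understated by √(0.1161/0.1735) = 0.82. The effective cut-off is 1.96 × 0.82 = 1.60, a two-sided error of about 11%.
- NXTC more variable: true variance = 4/51 + 1/26 = 0.1169. Pooled variance = (50 × 4 + 25 × 1)/75 = 3, and 3 × 0.0581 = 0.1742. The factor is 1.22 and the cut-off 2.39, an error of about 1.7%.

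**Simulated type I error.** Equal means, normal data, 51 v 26, 20,000 trials per setting. The plan's rule is read as a mean-centred Levene test at 5%, then pooled t or Wilcoxon.

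| NXTC/other SD ratio | Pooled t | Wilcoxon | Plan's rule | Welch |
|---|---|---|---|---|
| 0.5 | 10.6% | 8.4% | 8.5% | 4.9% |
| 0.67 | 8.5% | 7.0% | 7.2% | 5.0% |
| 0.8 | 6.9% | 6.2% | 6.5% | 5.0% |
| 1 | 5.1% | 4.9% | 5.0% | 5.0% |
| 1.25 | 3.5% | 4.2% | 3.7% | 4.9% |
| 1.5 | 2.5% | 3.6% | 3.2% | 4.9% |
| 2 | 1.9% | 3.5% | 3.4% | 5.2% |

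Repeat runs agree to within about 0.4 points. At 64 v 32 the plan's rule gives 8.4%, 7.0%, 6.6%, 5.1%, 3.9%, 3.3% and 3.5%, so the dropout assumption does not drive the result. At 26 v 26 the plan's rule stays at 4.8-5.6%.

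**Power for 0.95 points, 51 v 26.** With placebo SD assumed 1.19:

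| NXTC/placebo SD ratio | Plan's rule | Welch |
|---|---|---|
| 1 | 90.5% | 90.2% |
| 1.1 | 87% | 88% |
| 1.25 | 81% | 84.5% |
| 1.5 | 71% | 79% |
| 2 | about 51% | about 63% |

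An SD of 1.19 gives 90% at equal spread, above the stated 80%. If the SDs are instead scaled so that the standard error corresponds to about 80%, the plan's rule against Welch gives 71% v 78% at ratio 1.5 and 69% v 79% at ratio 2. In the other direction it gives 81% v 78% at both 0.67 and 0.5.

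**How large a ratio could partial response produce?** Take placebo SD 1.19 and a mean effect of 0.95 carried by a fraction p of patients, each gaining 0.95/p. The added variance is p(1 − p)(0.95/p)².
- p = 0.5: 0.25 × 1.90² = 0.90. SD = √(1.416 + 0.903) = 1.52, ratio 1.28. Power is 79% for the plan's rule and 84% for Welch.
- p = 0.35: 0.2275 × 2.71² = 1.68. SD = √(1.416 + 1.676) = 1.76, ratio 1.48.

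**Skewed data (gamma, shape 2), 51 v 26, equal means.** Wilcoxon rejects 19.4% at ratio 0.5 and 12.5% at ratio 2. Welch rejects 5.8% and 4.7%.

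**The case against.** Several stronger readings are tempting, and the documents do not support them.

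- **That the Wilcoxon test needs equal spread to be valid.** It does not when treatment changes nobody: randomisation then gives identical distributions and the test holds its level. The error arises only for equal means with unequal spread. That case still matters, because the planned effect of 0.95 is most naturally a difference in means, and two different active prescriptions can have equal average effects without identical distributions.
- **That power is lost whichever arm varies more.** Nominal power falls only when NXTC is the more variable arm. In the other direction it is slightly above Welch, at the price of false positives.
- **That the switch to Wilcoxon creates the error.** For normal data the switch reduces it when spreads differ (10.6% to 8.4% at ratio 0.5). At modest ratios much of the error comes from the pooled t-test that a Levene test usually leaves in place: at ratio 1.25, pooled t gives 3.5%, Wilcoxon 4.2%.
- **That false positives against placebo are to be expected.** Varied drug response makes NXTC the more variable arm, where the rule is conservative. The 7-9% figures need the smaller arm to vary more, which is more plausible against BHG or YTG.

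It is also fair to say that the article names neither a Levene test nor a cut-off, that a fuller analysis plan may exist, that the trial is described as a pilot, and that BHG and YTG against placebo are 1:1. These limit the size of the point. They do not remove it: the article does name its tests, and none of them suits a 2:1 comparison of means with unequal spread.

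**Conclusion.** The point holds in a limited form. In the three 2:1 comparisons with NXTC, the two listed tests do not hold 5% for a difference in means when spreads differ, and the unequal-variance t-test that would is absent. The departure is small at SD ratios between 0.8 and 1.25 (3.7-6.5%) and material beyond that (7-9% at 0.67 to 0.5, 3-3.5% at 1.5 to 2). The power cost applies only if NXTC is the more variable arm: about 4 points at ratio 1.25, 8 at 1.5 and 12 at 2.

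All of this rests on assumed SDs, normal data and a Levene reading of the rule. The article does not show that spreads will differ, so it cannot be said that the NXTC comparisons will have the wrong error rate. The change is worth making because it protects against that possibility at almost no cost.

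**What to change.** In the Statistical Analysis Plan section, name the Welch t-test as the method for between-group comparisons of mean change in quantitative outcomes, used from the outset and without a preliminary variance test. A Levene step leading to Welch is less exact (4.0-6.3% in the 2:1 settings). If a regression model is used, specify heteroscedasticity-robust standard errors instead. Do not use the Wilcoxon test as the remedy for unequal variance; keep it as a supporting analysis for markedly non-normal data.

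The cost is a sentence of text, under 1 point of power when SDs are equal, and some less favourable p-values when the smaller arm is the more variable one.
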